### 4.6 Data reconciliation

To minimise bias, radiological data identifying progressors and non-progressors will be blinded from those performing the concurrent molecular analysis.

#### 4.6.1 Precision for detection of significant changes in the molecular characteristics

Data from radiological progressors and non-progressors will allow us to populate the contingency table. We will statistically derive the minimum precision for significance of changes in molecular characteristics needed to maintain the association between radiological and molecular progression.

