#### 4.4.1 Molecular index

We will use next-generation sequencing and expression analyses to derive a quantitative molecular index for every baseline (MolBL) and follow-up (MolFU) biopsy. For each individual patient, the difference in the baseline molecular index between the two baseline biopsy samples (ΔMolBL) will be calculated. This is a measure of intrinsic patient tumour heterogeneity and will identify molecular features which are consistent between lesions, overcoming sampling bias. The relationship of the targeted biopsy sample to the longitudinal axis of the cancer lesion will also be taken into account using multi-slice processing and separate processing of the sample extremities.

We will use the same metrics to generate a MolFU for each patient using per protocol follow-up biopsy samples. We will then compare MolBL and MolFU for every individual patient and extract a ΔMolBL:MolFU score. Patients will be classified as having a molecular progression event if the ΔMolBL:MolFU score is greater than 95% CI of the combined ΔMolBL scores. Researchers generating the molecular index score will be blinded to radiological progression annotations.

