#### 4.6.2 Determination of molecular progressors

Precision will be applied to changes in molecular characteristics to determine significant variation between baseline and follow up molecular indices for every studied parameter derived from the molecular analysis.

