### 8. Statistical analysis

The primary statistical analysis will be to estimate the association of match‐paired binary responses (molecular and radiological progressors) since the results of the two tests are not independent. For McNemar’s test of paired proportions using the Miettinen normal approximation with a two‐sided significance level of 0.05, a sample size of 60 achieves a power of at least 0.8 when the discordant proportions are 0.05 (5%) and 0.25 (25%) of the total number. The ratio of progressors will inform the precision of the IC for the molecular analysis. Study results will be shared in peer reviewed journal articles.

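### Two conflicting rules define a molecular progressor, and one of them sets the threshold by reference to the radiological result it will be compared with

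*Protocol article*

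**What the plan says.** The article describes the molecular classification in two ways.

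**Rule A, independent of radiology.** The abstract (Methods) and section 4.4.1 call a participant a molecular progressor when the baseline-to-follow-up score lies above the 95% CI of the combined differences between paired baseline biopsies. Section 4.4.1 adds: "Researchers generating the molecular index score will be blinded to radiological progression annotations". Sections 4.3 and 4.6 also promise mutual blinding of the molecular and radiological assessments, and section 4.6 gives reduction of bias as the reason.

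**Rule B, informed by radiology.** Section 4.6.1 fills the contingency table from radiological status and continues: "We will statistically derive the minimum precision for significance of changes in molecular characteristics needed to maintain the association between radiological and molecular progression". Section 4.6.2, whose heading says that it determines the molecular progressors, states: "Precision will be applied to changes in molecular characteristics to determine significant variation between baseline and follow up molecular indices for every studied parameter". Section 4.3 has a similar sentence about keeping the association for a given precision. Section 8 adds: "The ratio of progressors will inform the precision of the IC for the molecular analysis"; the article does not expand the abbreviation IC.

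The primary outcome (section 7.1) is the proportion of concordant molecular and radiological progressor pairs. Section 8 analyses the same two binary labels with McNemar's test. The article does not say whether rule A or rule B supplies the molecular label.

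**The concern.** A label that is to be compared with radiology should be fixed without looking at radiology. Under rule B as written, the criterion for the molecular threshold is the association itself, and the same participants then supply the primary result. A reported association or concordance would then reflect partly how the threshold was chosen and partly biology, and the two could not be separated afterwards.

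The blinding in sections 4.3, 4.4.1 and 4.6 exists to prevent this. Even if laboratory staff never see a radiology report, a molecular label whose threshold was set using radiological outcome is no longer an independent assessment.

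The rules also differ in scope. Rule A works on one index score per participant, while section 4.6.2 speaks of every parameter studied.

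**Working it through.** **1. The plan's own figure.** Section 8 plans McNemar's test under Miettinen's normal approximation at two-sided 0.05. It claims that "a sample size of 60 achieves a power of at least 0.8", taking the two discordant cells to hold 5% and 25% of participants.

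- Total discordance ψ = 0.05 + 0.25 = 0.30; difference d = 0.25 − 0.05 = 0.20; n = 60; z = 1.96.
- Power = Φ{[d√(nψ) − zψ] / √[ψ² − d²(3 + ψ)/4]}
- = Φ{[0.20 × √18 − 1.96 × 0.30] / √[0.09 − 0.04 × 3.30/4]}
- = Φ{(0.8485 − 0.5880) / √0.057} = Φ(1.09) = 0.862.

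The stated power of at least 0.8 is reproduced, and the sample size is not in question.

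**2. The two rules side by side.**

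| | Rule A (abstract, 4.4.1) | Rule B (4.6.1, 4.6.2; echoed in 4.3, 8) |
|---|---|---|
| Data that set the threshold | Paired baseline biopsies | Contingency table holding radiological status |
| Criterion | Exceeds baseline heterogeneity | Association is maintained |
| Applied to | One index score | Every studied parameter |
| Needs radiology? | No | Yes |

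Both cannot supply the primary label.

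**3. Rule B read as a search for a supportive cut.** Assumptions, none of them in the article: 60 participants, a molecular score unrelated to radiology, radiological progression in 15 to 40%, and the cut chosen between 10% and 90% molecular progressors to give the strongest association (uncorrected chi-square, nominal two-sided 0.05). By simulation with no true association:

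| Cut-off | Positive association declared | Either direction |
|---|---|---|
| Fixed in advance, 20% molecular progressors | about 3–4% | about 4–5% |
| Best cut, searched over 10–90% | about 20% (18–21%) | about 35–41% |

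**4. Rule B read as matching counts.** The sentence in section 8 on the ratio of progressors could mean setting the cut so that molecular progressors are as many as radiological ones. Let both counts be k, with a participants positive on both.

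- Discordant cells: b = k − a and c = k − a, so b = c.
- McNemar statistic: (b − c)²/(b + c) = 0 in every data set.
- The design alternative, a difference of 0.25 − 0.05 = 0.20 between the margins, cannot occur.
- The chi-square test of association stays at about 5% two-sided, so it is not inflated.

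**5. Effect on the concordance proportion.** Take 30% radiological progressors and no association.

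- Fixed cut at 20% molecular progressors: expected concordance 0.20 × 0.30 + 0.80 × 0.70 = 0.62.
- Cut chosen to maximise concordance between 10% and 90%: simulated mean 0.67.
- Simply moving the cut to 10%, with no search: 0.10 × 0.30 + 0.90 × 0.70 = 0.66.

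Most of the rise from 0.62 to 0.67 therefore comes from the changed share of molecular progressors. At the cut with the strongest association, concordance was not consistently higher than at the fixed cut.

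**The case against.** The strongest reply is that the only explicit definition of a molecular progression event is rule A, which appears twice. Sections 4.6.1 and 4.6.2 are vague and give no algorithm, and a ratio of progressors is a marginal count, not a set of patient-level labels. This stands as far as size goes: the search in step 3 is one construction of rule B, and under the matching reading the association test is not inflated. It does not remove the conflict. Section 4.6.1 names the association as its criterion, and section 4.6.2 is presented as the step that determines the molecular progressors.

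A reader might infer more than the documents support:

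- **That the planned test has a false-positive rate of about 20%.** That rate is for a chi-square test of association. McNemar's test compares the two marginal proportions, and its result depends on how many participants the cut makes positive: no rejections when counts are matched, but rejection in most data sets at the best-association cut.
- **That concordance is necessarily biased upward.** Step 5 does not show this.
- **That blinding is broken.** No blinded person is said to see radiology. A separate analyst could set the threshold after the index values are generated. What is lost is the purpose of the blinding, not necessarily its observance by any individual.
- **That testing every parameter gives each participant many chances to be flagged.** This needs a rule that one positive parameter suffices. None is stated, and section 4.4.1 describes a single index, so no multiplicity rate can be attached.
- **That no validation is planned.** The article condenses a fuller protocol that is not shown, so silence here proves nothing.

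**Conclusion.** The concern holds as a conflict of definitions for the primary label, one of which is informed by the outcome. Followed as written, sections 4.6.1 and 4.6.2 make the molecular classification depend on radiological status in the same participants, contrary to the abstract and section 4.4.1 and to the aim of the blinding.

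The size cannot be fixed from the article, because neither the algorithm nor the radiological progression rate is given. A best-cut search raises false positive associations from about 3–4% to about 20% under the assumptions in step 3. Matching the counts leaves the association test intact but makes the planned McNemar test incapable of rejecting. On either reading the choice of threshold partly determines the primary result. The stated sample size and power are unaffected.

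**What to change.** 1. State in sections 4.4.1 and 8 that the primary molecular classification uses only a rule of the section 4.4.1 type: one molecular index, with a threshold built from within-patient baseline differences and no radiological data.
2. Lock the cut-off and every participant's molecular label, with a date, before linkage to radiological status.
3. Amend sections 4.6.1 and 4.6.2, the related sentence in section 4.3 and the sentence on the ratio of progressors in section 8, so that any radiology-informed cut-off or per-parameter analysis is labelled exploratory. Give it a permutation p-value in which radiological labels are shuffled and the whole cut-off search is repeated each time.

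No extra participants, samples or visits are needed, and the sample size stands. The cost is wording, a documented lock, and the loss of freedom to tune the threshold in the primary analysis. Section 4.8 reports only 5 participants through active follow-up when the article was written, so at that stage a lock before linkage was still practicable.

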#### 4.6.2 Determination of molecular progressors

Precision will be applied to changes in molecular characteristics to determine significant variation between baseline and follow up molecular indices for every studied parameter derived from the molecular analysis.

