**Methods:**

RECONCILE is an ethics approved (20/LO/0366) single centre, prospective, longitudinal, observational cohort study of recently diagnosed (within 12 months), organ-confined Gleason 3 + 4 cancers (MCCL ≤10mm) currently under active surveillance. 60 treatment-naïve participants with a concordant MRI lesion (Likert score 4 or 5) and PSA ≤ 15 ng/ml will be recruited.

Blood, urine and targeted prostate tissue cores will be subject to next generation sequencing at baseline and one year in all participants. Semen will be collected from a specified sub-population. Baseline and interval MR images will be extracted from standard of care prostate MRI ahead of radiomic analysis. Data extracted from radiological and biological samples will be used to derive the association of molecular change and radiological progression, the primary outcome of the study.

To compensate for spatial intratumoral heterogeneity and inherent sampling bias, a molecular index will be derived for each participant using the molecular profile of tumour tissue at both baseline (MolBL) and one year (MolFU). We will extract a ΔMolBL:MolFU score for each participant. Molecular progression will be defined as a MolBL:MolFU score >95% CI of the combined ΔMolBL scores. Radiological progression is defined as a PRECISE score of 4 or 5. The study is powered to detect an association with a statistical power of 80%.

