Access to standard of care diagnostic biopsy tissue will be sought once the NHS centre has completed all necessary diagnostic evaluation. Formalin-fixed paraffin-embedded (FFPE) tissue blocks and haematoxylin and eosin (H&E) stained slides will be requested by RECONCILE study staff and anonymised H&E slides will be scanned using high resolution scanners and uploaded to the RECONCILE digital pathology database. Slices from standard of care FFPE tissue blocks will be collected in line with study standard of care operating procedures before returning all slides and blocks to the relevant NHS pathology department.

*Analyses*

Blood components (white blood cells, plasma, serum), urine, tissue and semen will undergo molecular analysis including genomic, mRNA expression and protein studies. These will include, but are not limited to, next-generation sequencing, whole-genome micro-array expression profiling, immunohistochemistry and immunofluorescence and ELISA tests.

*Long-term healthcare data linkage*

Consent will be sought to obtain long-term patient outcomes from national health records such as the Office for National Statistics, NHS Digital, Public health England and other applicable NHS information systems or national databases.

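### Sections 4.4.1 and 4.6.2 give different bases for calling a man a molecular progressor, and the primary outcome needs exactly one call per man

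*Protocol article*

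**What the plan says.** Section 4.4.1 sets out to "derive a quantitative molecular index for every baseline (MolBL) and follow-up (MolFU) biopsy". It then compares the two time points to give one ΔMolBL:MolFU score per man and fixes the rule: "Patients will be classified as having a molecular progression event if the ΔMolBL:MolFU score is greater than 95% CI of the combined ΔMolBL scores". The abstract repeats it: "Molecular progression will be defined as a MolBL:MolFU score >95% CI of the combined ΔMolBL scores". This is one score against one limit, and the limit comes from the spread between the two baseline cores.

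Section 4.6 returns to the same classification. Section 4.6.1 first fills the contingency table with the radiological groups and then states: "We will statistically derive the minimum precision for significance of changes in molecular characteristics needed to maintain the association". Section 4.6.2 applies that precision "to determine significant variation between baseline and follow up molecular indices for every studied parameter derived from the molecular analysis".

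Section 4.3 builds a table of R+ or R- against M+ or M-. Section 7.1 makes the primary outcome the share of men in whom the two calls agree, and section 8 analyses the pairs with McNemar's test in 60 men. Each of these needs a single M+ or M- per man.

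**The concern.** The two sections differ in two respects. The unit changes from one composite score to an index for each parameter. The source of the limit changes from the baseline spread (4.4.1) to a precision worked out once radiological status is known (4.6.1). Neither section refers to the other or says which governs.

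If section 4.6.2 were applied as worded, parameter by parameter, two things could follow. Each parameter could give its own 2x2 table, and the primary result would then depend on which table is reported. Alternatively, the parameter-level calls could be merged into one, and a permissive merging rule would raise the share of unchanged men labelled M+. Because McNemar's test compares the M+ proportion with the R+ proportion, a shift in the M+ proportion alone moves the result.

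**Working it through.** **The plan's own figure.** Section 8 gives N = 60, two-sided alpha 0.05, discordant proportions 0.05 and 0.25, and power of at least 0.8. With ψ = 0.05 + 0.25 = 0.30 and d = 0.25 − 0.05 = 0.20, the Miettinen approximation is

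power = Φ{[√(Nψ)·d − 1.96·ψ] / √[ψ² − d²(3 + ψ)/4]}.

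- Numerator: √18 × 0.20 − 1.96 × 0.30 = 0.8485 − 0.5880 = 0.2605.
- Denominator: √(0.09 − 0.033) = 0.2387.
- Power = Φ(1.09) = 0.86.

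The stated figure holds; 52 men would give 0.80. The calculation takes the discordant proportions as given, and they depend on how M+ is called.

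**The two rules side by side.**

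| | 4.4.1 and abstract | 4.6.1 and 4.6.2 |
|---|---|---|
| Unit | one ΔMolBL:MolFU score per man | "molecular indices for every studied parameter derived from the molecular analysis" |
| Limit | from the combined ΔMolBL scores | a precision tied to the association with radiological progression |
| Calls per man | one | not stated |

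**Size under an illustrative rule.** The following are assumptions, not figures from the article:
- a man is M+ if any one of k parameters exceeds its limit;
- parameters are independent;
- each limit is exceeded in 5% of unchanged men, or in 2.5% if only the upper end of a 95% range counts;
- k is 10 or 20.

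P(false M+) = 1 − (1 − a)^k.

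- k = 10: 1 − 0.975^10 = 0.224; 1 − 0.95^10 = 0.401.
- k = 20: 1 − 0.975^20 = 0.397; 1 − 0.95^20 = 0.642.

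With k = 1 the rate is 2.5% or 5%. The 50% mark is passed at k = 14 (5% limit) or k = 28 (2.5% limit).

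**Effect of correlation.** With equicorrelated normal parameters:

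| Correlation | k = 10: 2.5% / 5% limit | k = 20: 2.5% / 5% limit |
|---|---|---|
| 0.3 | 17.8% / 30.7% | 28.0% / 44.5% |
| 0.5 | 14.4% / 24.7% | 21.0% / 33.9% |
| 0.8 | 8.6% / 15.2% | 11.2% / 19.0% |

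At a 5% limit, passing 50% takes 26 parameters at correlation 0.3, 63 at 0.5 and about 5,000 at 0.8.

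**Effect on the primary table.** Suppose M and R are unrelated and 20% of men are R+ (assumed). With 5% M+, the discordant cells are M+R- = 0.05 × 0.80 = 0.04 and M-R+ = 0.95 × 0.20 = 0.19. With 50% M+, they are 0.50 × 0.80 = 0.40 and 0.50 × 0.20 = 0.10. The larger discordant cell changes sides. The same happens at 10% or 30% R+.

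**If each parameter has its own table.** The false M+ rate per table stays at 2.5% or 5%, and the problem becomes multiple testing. The tables share the same radiological status, so the independence formula does not size it.

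**The case against.** The strongest defence is that section 4.4.1 governs. Its rule is explicit and repeated in the abstract, and section 7.2 cites 4.4.1 as the definition of the index. The plural indices in 4.6.2 may simply mean the two time points, and the parameters may be components that feed the index. This reading is possible, but 4.6.2 does not state it. It also leaves the second difference in place, because a precision derived under 4.6.1 is not the limit of 4.4.1.

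A reader might infer that section 4.6.2 would label most unchanged men as progressors. The article does not support that. It states no any-one-parameter rule and gives no number of parameters, and correlated molecular data could keep the rate well below one half. Nor can the breadth of assays in section 5.2 ("next-generation sequencing, whole-genome micro-array expression profiling, immunohistochemistry and immunofluorescence and ELISA tests") stand in for that number. The list covers blood, urine, tissue and semen together, whereas the index of 4.4.1 uses biopsies, by sequencing and expression analyses. Even the single-score rate of 2.5% to 5% assumes that the 95% CI acts as a reference range for individual men.

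Two further defences carry less weight. Those generating the index are blinded to radiological progression (4.4.1, 4.6), which protects the measurements but does not fix which parameter or limit is used once the data are joined. And a condensed article may leave a combining rule to the full protocol or analysis plan. That is fair, but the point here is that the article prints two bases for the same call, not that detail is absent.

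**Conclusion.** The inconsistency stands on the text alone: one classification, two units and two sources for the limit, with no statement of which applies. It should be corrected because the call is half of the primary outcome and the power statement depends on it.

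The inflation of about 22% to 40% at 10 parameters and 40% to 64% at 20 is an illustration, not a property of the plan. It rests on an any-one-parameter rule, independence, a 2.5% to 5% limit per parameter and an assumed number of parameters. Correlation lowers it, and separate tables would turn it into a multiplicity problem. If parameters only feed the single index, neither harm arises, but the article would need to say so.

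**What to change.** State in section 4.6.2 that M+ or M- for the primary outcome comes only from the single ΔMolBL:MolFU score of section 4.4.1. State that the index and its cut-off are locked before linkage to the PRECISE results, and bring the precision of section 4.6.1 into line with that. Move changes in individual parameters to the secondary mechanistic analyses, with false-discovery-rate control.

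The cost is wording in the protocol and analysis plan. Section 4.8 reports only 5 men through active follow-up at the time of writing, so no data collection is affected. The downside is that a change in a single parameter no longer contributes separately to the primary call.

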### 4.7 Patient and public involvement

The RECONCILE study was originally conceived as a work stream of the ReIMAGINE Risk study and was included in the patient and public involvement (PPI) consultation that took place for this. The study design (including the number of visits and outcome measures) and all patient facing documents have been reviewed by two PPI committees, first the ReIMAGINE PPI committee consisting of patients and members of the wider public who have been affected by, or have experience of, prostate cancer and second, the South East London Consumer Research Panel for Cancer.

### 4.8 Phase of trial

RECONCILE is a single site study which opened to recruitment in July 2020 (n = 62). So far, 10 participants have been identified as non-evaluable. A replacement will be recruited for each non-evaluable case. Recruitment is expected to complete in July 2022. 37 participants have donated baseline samples, and 5 participants have completed active study follow up.

## 5. Study schedule

### 5.1 Screening and recruitment

Potential participants will be identified at the time of referral for tertiary multidisciplinary team review, during routine outpatient clinic, or following participation in the ReIMAGINE Risk study. Relevant NHS multidisciplinary team meetings (MDT) and recruitment logs to the ReIMAGINE Risk study will be screened weekly by study staff for potential participants. All eligible participants will be offered enrolment.

The first approach of eligible participants will take place over the telephone, or in an NHS clinic. A participant information leaflet (PIL) and other relevant study documentation will be provided to interested patients who meet study inclusion and exclusion criteria (Table 1). Consent is written and can be given over the telephone (with relevant signed documents returned by post) or during a face to face clinical visit.

All those approached or considered for recruitment will be recorded on the study screening log. Participants will consent to sharing of data from ReIMAGINE and PLiS (where applicable), donation of prostate tissue cores, blood, urine (and semen for those enrolled in the PLiS study), and healthcare data linkage.

